**Late Postoperative Complication Incidence Rate (31 days to 2 years postoperatively)**

[Definition]

Describe complications occurring between 31 days and 2 years postoperatively, using the analysis population as the denominator. The following complications (Table D) are specifically highlighted; their frequency and rates are documented.

When a complication occurs, the following details must be recorded in the medical records and case report: complication name, outcome, management of the complication, relationship to cervical spine surgery, treatment details/date of treatment, and whether hospitalization was prolonged.

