| Early Postoperative Complications/Adverse Events (within 30 days postoperatively) | | Confirm the presence of adverse events through medical history and physical examination.  If an adverse event occurs, document the event name, onset time, outcome, severity (including whether reoperation was required), relationship to cervical spine surgery, treatment details/date of treatment, and whether hospitalization was extended. | |
| Medical History/Physical Examination | | Conduct medical history and physical examination during regular postoperative outpatient visits. | |
| Plain X-ray | | Cervical spine (AP/Lateral/Anterior flexion lateral/Posterior flexion lateral): Confirm C2-7 angle/C-SVA/C7 slope  Full spine standing (AP/Lateral): Confirm SVA/Lumbar lordosis angle/Thoracic kyphosis angle/Pelvic incidence, check for existing vertebral fractures | |
| Cervical Plain CT | | Horizontal, sagittal, and coronal slices at each intervertebral level: Confirm presence of OPLL/Lamina retention rate, hinge fractures/gutter bone union. | |
| Cervical Plain MRI | | T2 and T1 sagittal/horizontal images  Preoperative: Maximum stenosis level, presence of intramedullary signal changes, C4/5 paraspinal muscle area, dural sac area  Postoperative: C4/5 paraspinal muscle area, dural sac area, Grading of the mass posterior to the dural sac | |
| Late Postoperative Complications/Adverse Events (From 31 days post-op to within 2 years post-op) | | If an adverse event occurs, document: event name, onset timing, severity, outcome, seriousness (whether reoperation required), relationship to cervical spine surgery, treatment details/date, and hospitalization status. | |
| Outcome Investigation | | Survival (Last confirmed survival date, presence/absence of death, date of death, cause of death)  Reoperation (Reoperation presence/absence, reoperation date, reason for reoperation, reoperation method)  Study Discontinuation (Discontinuation presence/absence, discontinuation date, reason for discontinuation) | |
| Direct Medical Costs | | Hospitalization Costs (Medical fees excluding surgery, surgery-related costs [surgery, surgical drugs, anesthesia, anesthetic drugs])  Outpatient Costs (Consultations, tests, drugs, other)  Hospitalization Re-treatment Costs for Adverse Events (Hospitalization medical fees excluding surgery, surgery-related costs [surgery, surgical drugs, anesthesia, anesthetic drugs])  Research collaborators collect the above costs from medical claims. | |

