**8.1.2　Secondary endpoint**

(1) Operative time

(2) Estimated blood loss

(3) Proportion achieving the MCID for recovery in cervical JOA score at postoperative 1 and 2 years

(4) Health-related QOL (EQ-5D) at postoperative 1 and 2 years

(5) Severity of neck pain, upper limb pain, and upper limb numbness (VAS) at postoperative 1 and 2 years

(6) NDI at postoperative 1 and 2 years compared to preoperative

(7) Retention rate of expanded lamina at postoperative 1 and 2 years ^3)^

(8) Proportion of hinge fractures at postoperative 1 and 2 years

(9) Percentage of gutter bone union at postoperative 1 and 2 years^4)^

(10) Cervical spine alignment at 1 and 2 years post-surgery (C-SVA, C2-7 angle, C7 slope)

(11) Paraspinal muscle cross-sectional area (C4/5 level) at postoperative 1 and 2 years

(12) Dural sac area (C3/4, C4/5, C5/6, C6/7 levels) at postoperative 1 and 2 years

(13) Grading of the mass posterior to the dural sac at postoperative 1 and 2 years

(14) Incremental Cost-Effectiveness Ratio (ICER)

(15) Surgical Complication Rates

・Intraoperative complication rate (from start of surgery to completion/closure)

・Early postoperative complication rate (from completion/closure to within 30 days postoperatively)

・Late postoperative complication rate (from postoperative day 31 to within 2 years)

・Mortality rate (entire period: includes non-surgery-related deaths)

・Reoperation rate within 2 years

*For evaluating intraoperative/postoperative complications, use the evaluation criteria from the Japanese Society for Spine Surgery and Related Research database (JSSR-DB) (<https://ssl.jssr.gr.jp/db/>).

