**10.1.2　Safety Analysis Set (SAS)**

This is defined as the population of all cases enrolled and randomized in this study who underwent the protocol treatment (cervical laminoplasty).

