**10.2　Target Enrollment Numbers and Rationale**

Target enrollment: 216 cases

(Control group [mini-plate]: 108 cases, Test treatment group [suture-anchor]: 108 cases)

[Rationale]

Regarding the primary endpoint, the recovery rate in cervical JOA scores before and after surgery, a retrospective pilot study at Saiseikai Kawaguchi General Hospital, which used a patient population similar to this study, reported rates of 49.9±22.8% (21 cases) for the plate method and 52.6±32.9% (20 cases) for the suture anchor method (unpublished data).

Furthermore, a previous report^3)^ indicated that the MCID for compressive myelopathy is 52.8%. Based on the pilot study and past MCID findings, the recovery rate in cervical JOA scores for the control group (plate method) in this study was set at 50% (standard deviation 40%), with a non-inferiority margin of 20%. With a significance level (one-sided) of 0.025 and

and a power of 0.9, the required sample size for both groups combined is 172 cases. Anticipating approximately 20% dropout, the target sample size for both groups combined was set at 216 patients.

This target enrollment number is treated as an anticipated enrollment number, and exceeding this anticipated number is permitted. However, the Principal Investigator (PI) shall manage the cumulative actual enrollment numbers across all participating institutions to ensure the total number of cases does not exceed the study's target enrollment. If additional enrollment is required to meet the overall study target, prior approval must be obtained from the Ethics Review Committee or equivalent body.

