**10.4　Data Handling**

Data handling during data collection and analysis shall generally follow the principles outlined below. In case of doubt, the principal investigator and the person responsible for statistical analysis shall consult and decide. Missing values shall not be imputed. Details shall be specified separately in the statistical analysis plan.

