For FAS subjects, perform analyses similar to those for primary endpoints on the change in each evaluation item from preoperatively to 1 year postoperatively.

Additionally, perform analyses similar to those for secondary endpoint (2) on the change in each evaluation item from preoperatively to 1 and 2 years postoperatively.

(11) Paraspinal muscle cross-sectional area (C4/5 level) at postoperative 1 and 2 years

For FAS, perform the same analysis as for primary endpoints on the change in paraspinal muscle cross-sectional area from preoperatively to 1 year postoperatively.

Additionally, perform the same analysis as for secondary endpoint (2) on the change in paraspinal muscle cross-sectional area from preoperatively to 1 and 2 years postoperatively.

(12) Dural sac cross-sectional area (C3/4, C4/5, C5/6, C6/7 levels) at postoperative 1 and 2 years

For FAS subjects, perform the same analysis as for the primary endpoint on the change in dural canal area from preoperative to 1-year and 2-year postoperative time points.

Additionally, perform the same analysis as for secondary endpoint (2) on the change in dural canal area from preoperative to 1-year and 2-year postoperative time points.

(13) Grading of the mass posterior to the dural sac at postoperative 1 and 2 years

For FAS subjects, classify posterior spinal canal compression at 1 and 2 years postoperatively into mild (Grade 1-3) and severe (Grade 4-5). Calculate the proportion of severe posterior spinal canal compression at 1 and 2 years postoperatively by group. For between-group comparisons, calculate the difference in the proportion for each evaluation item and its 95% confidence interval, then perform Fisher's exact test. Use the Clopper-Pearson method to calculate the confidence interval.

(14) Incremental Cost-Effectiveness Ratio (ICER)

Calculate the ICER of the test treatment group relative to the control group.

Refer to Section 8.1.2 for details on the calculation method.

(15) Surgical complication incidence

For SAS, calculate the number of cases and rates of each complication by the following categories for each assigned group.

・Intraoperative complication rate (from start of surgery to end of surgery (wound closure))

・Early postoperative complication rate (from end of surgery (wound closure) to within 30 days postoperatively)

・Late postoperative complication rate (from postoperative day 31 to within 2 years postoperatively)

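### The late complication rate (day 31 to 2 years) keeps every operated patient in the denominator, so patients lost before 2 years count as event-free and the 2-year risk is underestimated

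*Protocol*

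**What the plan says.** Protocol 8.2 (15), under the late postoperative complication rate, fixes the denominator: "Describe complications occurring between 31 days and 2 years postoperatively, using the analysis population as the denominator".

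Protocol 10.5.3 (15) names the population and the summary: "For SAS, calculate the number of cases and rates of each complication by the following categories for each assigned group". The late category there runs from postoperative day 31 to 2 years.

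Protocol 10.1.2 defines that population: "This is defined as the population of all cases enrolled and randomized in this study who underwent the protocol treatment (cervical laminoplasty". Nothing in the definition depends on how long a patient was followed.

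Protocol 10.2 on expected loss: "Anticipating approximately 20% dropout, the target sample size for both groups combined was set at 216 patients". It does not say when the loss occurs or how much of it precedes surgery.

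Protocol 10.4 adds: "Missing values shall not be imputed".

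Protocol 8.1.2 also lists "Reoperation rate within 2 years" as part of the same secondary endpoint. Section 8.2 (15) says that it is recorded separately from the complication categories, and the list in 10.5.3 (15) does not include it. No denominator is given for it anywhere.

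**The concern.** A proportion over a fixed set of patients estimates a 2-year risk only if everyone in the denominator was observed for 2 years or had the event before leaving. Here the denominator includes patients whose observation stops early. Their unobserved time is treated as event-free time. In effect this fills in a value of no event for each of them, which sits awkwardly with the rule in 10.4 against imputation.

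The intraoperative and 30-day rates are hardly exposed to this. The late rate is: its window spans 699 days, and after the 30-day visit the schedule in 7.2.1 has study visits only at 1 and 2 years.

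The matter deserves attention because the objective in section 4 covers safety as well as efficacy. Late loosening or displacement, neurological symptoms and worsening kyphosis (Table D in 8.2) are the harms on which the two fixation methods could differ. The trial is open-label, so loss can differ between arms.

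**Working it through.** **Step 1. The plan's own figures.** Inputs from 10.2: SD 40, margin 20, one-sided alpha 0.025, power 0.9; the true difference is taken as 0.
- Normal approximation: 2 × (1.960 + 1.282)² × 40² / 20² = 84.1, so 85 per arm (170 in total).
- Noncentral t: 86 per arm, 172 in total, power 0.903. This matches the stated 172.
- Dropout: 86 / (1 − 0.20) = 107.5, so 108 per arm and 216 in total. This also matches.

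The 20% is thus the plan's own planning figure. It was applied to enrolled patients, for a 1-year endpoint.

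**Step 2. Formula for the crude rate.** Let R be the true late risk over days 31 to 730, d the share of the safety set lost before 2 years, and F(u) the risk accrued by fraction u of the window. If loss is unrelated to the event:

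crude rate = (1 − d) × R + d × mean of F at the time of loss

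relative understatement = 1 − crude rate / R

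F lies between 0 and R, so the understatement lies between 0 and d whatever the shape of the hazard.

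**Step 3. Numbers.** Assumed: R = 10% (the documents give no late rate), d = 20%, and a constant hazard, so F(u) = 1 − 0.9^u. For even loss, mean F = 1 − 0.10 / 0.1054 = 0.0509, and the crude rate is 0.8 × 0.10 + 0.2 × 0.0509 = 0.0902.

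| When the 20% leave | Crude rate | Relative understatement |
|---|---|---|
| All at day 31 | 8.0% | 20% |
| Evenly in the first half of the window | 8.5% | 15% |
| Evenly over the window | 9.0% | 10% |
| All at 1 year | 9.0% | 10% |
| Evenly in the second half | 9.5% | 5% |
| All at the 2-year point | 10.0% | 0% |

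An assumed true risk of 5% or 20% changes the relative figures by less than half a percentage point.

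**Step 4. What moves the size.**
- Only 10% of the safety set lost, the rest of the dropout falling before surgery: 0% to 10%, about 5% with even loss.
- Early events (assumed F(u) = R × (1 − e^(−3u)) / (1 − e^(−3))), d = 20%: 5.6% with even loss, 1.4% with loss in the second half.
- 30% lost by 2 years, constant hazard: about 15% with even loss, at most 30%.
- 20% lost between day 31 and day 365, continuing at the same rate: cumulative loss hazard 0.223 × 699 / 334 = 0.467, so 1 − e^(−0.467) = 37% are lost by 2 years. The mean observed share of the window is 0.373 / 0.467 = 0.80, an understatement of about 20%.

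**Step 5. Between arms (even loss, constant hazard).**
- Equal loss of 20%, true risks 10% and 5%: crude 9.02% and 4.50%. The ratio stays at 2.00; the difference falls from 5.0 to about 4.5 points.
- Equal true risk of 10%, loss 25% against 15%: crude 8.77% and 9.26%, ratio 0.95.
- Equal true risk of 10%, loss 30% against 10%: crude 8.53% and 9.51%, ratio 0.90.

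In both unequal cases the arm with more loss looks safer although the true risks are the same.

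**The case against.** **The rate is descriptive.** No test, margin or between-arm contrast is attached to it, and a crude proportion over the safety set is a common safety summary. Further displays may be in the SAP, which is not at hand. This stands as a reason to keep the crude summary. It does not remove the point, because the protocol itself fixes the denominator and a reader will take the result as a 2-year risk.

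**The effect is small beside sampling error.** On an assumed 10% risk the shift is at most 2 points, while the 95% half-width with 108 patients per arm is 1.96 × √(0.10 × 0.90 / 108) = 5.7 points. True, but sampling error is shown by an interval and this bias is not. It always runs towards fewer complications.

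**More is seen than the two late study visits.** Section 7.2.2 mentions regular outpatient visits and costs taken from medical claims, and 7.4 asks participants to report symptoms. A missing 1-year JOA score does not mean that nothing is known about complications. This stands and may reduce the size. It does not help once contact has ended.

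**Stronger readings that the documents do not support.**
- A reader might infer that the rate is understated by at least 5%. No such floor follows: late losses, losses before surgery (those patients never enter the safety set) and early events all move the figure towards 0.
- A reader might take 20% as the loss from the safety set by 2 years. The figure concerns enrolled patients and the 1-year endpoint, so the true loss could be lower or higher.
- A reader might carry the same denominator over to reoperation. The protocol fixes none for it.

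**Conclusion.** The point holds as a downward bias in a secondary safety estimate. As written, the late complication rate underestimates 2-year risk whenever patients are lost before 2 years. The relative understatement is 0% to 20% if 20% of the safety set is lost, and about 10% if loss is even and the hazard constant. On an assumed true risk of 10% this is at most 2 percentage points, and about 1 in the even-loss case. It is smaller if part of the dropout precedes surgery or events come early, and larger if 2-year loss exceeds 20%.

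These figures assume that lost patients have the same risk as those who stay. That may fail, since 7.6 (5) ends participation for some patients because of an intraoperative complication.

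A reader might conclude that the trial's non-inferiority result is compromised. It is not: the primary analysis concerns the 1-year JOA recovery rate and does not use this denominator. With equal loss the between-arm ratio is also nearly unchanged. The comparison is distorted only if loss differs by arm, which is possible in an open-label trial but which nothing in the protocol predicts. The change is worth making because safety is part of the stated objective and the cost is low.

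**What to change.** In 8.2 (15) and 10.5.3 (15):

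1. Keep the number of cases and the crude proportion as a descriptive summary, including for the intraoperative and 30-day rates, where they are adequate.
2. For late complications, add per arm the number of patients followed to 1 year and to 2 years.
3. Add per arm the 2-year cumulative incidence of first late complication, censored at last contact, with death as a competing event (Aalen-Johansen), and the between-arm difference with a 95% CI. Define last contact as the last date on which complication status was known.
4. Use the same estimator for the 2-year reoperation rate, and so give it a stated method.
5. Align the recording lists for late complications in 8.2 and for adverse events in 9.1, which omit the date of onset, with 7.2.2, which includes onset timing.

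The data are already planned: 7.2.2 collects onset timing, reoperation date, discontinuation date, date of death and last confirmed survival date. The cost is wording, a little more analysis and slightly wider intervals. Two limits remain and should be stated with the results: events found only on scheduled imaging are dated by detection rather than onset, and censoring assumes that loss is uninformative, which cannot be verified.

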**Table D: Particularly Noteworthy Late Postoperative Complications**

| **Complication** | **Complication Details and Management** |
| --- | --- |
| Neurological Symptoms | Location (operated intervertebral space, adjacent intervertebral space, other location), responsible level, management, outcome |
| Local Kyphosis Worsening | Level, management, outcome |
| Slippage Worsening | Level, anterior/posterior, management, outcome |
| Systemic Complications | Name, Management, Outcome |
| Instrument-related | Loosening/Displacement, Management, Outcome |
| Infection | Superficial/Deep, Management, Outcome |
| Other | Complication Name, Management, Outcome |

**8.3** **Methods and Timing for Analyzing Evaluation Indicators**

Refer to “10. Matters Concerning Statistical Analysis”.

**９．Matters Concerning Recording, Reporting, etc. of Adverse Events, Surgical Complications, and Malfunctions**

**9.1** **Methods for Recording, Reporting, and Analyzing Adverse Events, Surgical Complications, and Malfunctions**

**１）Adverse Events**

An adverse event refers to any unfavorable or unintended injury or illness (including abnormal laboratory values) occurring in a research subject, regardless of whether it is causally related to the conducted study.

Symptoms or diseases present prior to registration shall be treated as pre-existing conditions and not considered adverse events. However, surgical complications (described later) are also included as adverse events. In this study, adverse events shall be categorized and tallied separately as intraoperative surgical complications, early postoperative complications (surgery-related/systemic complications), and late postoperative complications, as outlined in Table A to D in Section 8.2(9).

The evaluation period shall extend up to 2 years post-surgery.

When an adverse event occurs, the following details shall be recorded in the medical records and case report form: complication name, outcome, management of the complication, relationship to cervical spine surgery, treatment details/date of treatment, and whether hospitalization was prolonged. Additionally, the occurrence status shall be periodically compiled and recorded in the monitoring report.

**2) Surgical Complications**

Surgical complications in this study are defined as any undesirable or unintended illness or injury (including abnormal laboratory values) that occurs in study subjects in relation to the surgery performed as part of the protocol treatment. Surgical complications are classified as: general anesthesia complications; intraoperative complications (from the start of surgery to its completion [wound closure]); early postoperative complications (from completion of surgery [wound closure] to within 30 days postoperatively); and late postoperative complications (from 31 days postoperatively to within 2 years postoperatively). The evaluation period extends up to 2 years postoperatively.

When a surgical complication occurs, the complication name, outcome, management of the complication, severity, treatment details/date of treatment, and whether hospitalization was prolonged must be documented in the medical record and case report. Additionally, occurrence data must be periodically compiled and recorded in a monitoring report.

Severity is determined based on the Common Terminology Criteria for Adverse Events (CTCAE) version 5.0.

Grade 1: Mild, asymptomatic or mild symptoms, clinical or laboratory findings only, no treatment required

Grade 2: Moderate, requires minimal, localized, non-invasive treatment, limitations in activities of daily living beyond age-appropriate self-care

Grade 3: Severe or medically significant but not immediately life-threatening, requiring hospitalization or prolongation of hospitalization, incapacitation or inability to perform activities, limitation in activities of daily living

Grade 4: Life-threatening, requiring urgent intervention

Grade 5: Death due to the adverse event

1. **Serious Adverse Events and Surgical Complications**

The following are considered serious adverse events or surgical complications:

1) Death

2) Diseases or conditions that may lead to death

3) Diseases or conditions requiring hospitalization or extended hospitalization for treatment

4) Disability

5) Diseases or conditions that may lead to disability

6) Diseases or conditions deemed serious equivalent to 1) to 5)

7) Congenital diseases or abnormalities in subsequent generations

The evaluation period shall be up to two years post-surgery.

Event names, complication names, outcomes, responses to complications, treatment details/treatment dates, and whether hospitalization was extended shall be recorded in medical records and case reports. Occurrence data shall be periodically compiled and recorded in monitoring reports.

**４）Malfunctions**

A malfunction refers broadly to any poor condition of the device related to quality, safety, performance, etc., such as device damage or operational failure, regardless of whether it occurs during design, delivery, storage, or use. In this study, if an event qualifying as a malfunction occurs with the screws and mini-plates used in the control group (plate method) or with the suture anchors used in the test treatment group (suture anchor method), it shall be recorded in the medical records and case report forms. Additionally, the occurrence status will be periodically compiled and recorded in the monitoring report. Furthermore, as necessary, information regarding the malfunction will be shared with the manufacturer of the device (in a form that does not include personal information).

